### Statistical analysis

Descriptive analysis will be used to summarize the data. Specifically, results will contain statistics as mean, standard deviation, median, minimum and maximum values, whereas for categorical variables the frequency distribution tables with number of cases and percentage distribution will be presented. Statistical hypothesis testing procedures (*Kolmogorov–Smirnov* and *Shapiro–Wilk*) will be conducted for continuous variables to check, whether they satisfy the normality assumption. Given the fact that the response variable (SYNTAX score) presents a heavily-skewed and non-normal distribution with an excess number of zeros, non-parametric statistical hypothesis tests will be used for the investigation of the main effects of categorical variables on the population median values of the response variable. More specifically, the *Mann–Whitney* and *Kruskal–Wallis* followed by pair-wise comparisons through Mann–Whitney test using *Bonferroni’s correction* will be conducted. The investigation of the relationship between SYNTAX score and the set of continuous variables will be performed using the non-parametric *Spearman’s correlation coefficient*.

The model building process will be based on *Hurdle Models* that are a class of modeling techniques able to handle excess zeros and overdispersion of SYNTAX score variable. Describing briefly, the *Hurdle Model* has two parts: (*i*) a *zero hurdle part* which models the right-censored outcome SYNTAX score variable indicating patients with a zero-count ($$Y = 0$$) or patients with a positive count ($$Y = 1$$), where all values larger than zero are censored (i.e. fixed at one) and (*ii*) a *truncated count part* modeling the total number of SYNTAX score for patients presenting a non-zero count ($$Y > 0$$). Regarding the identification of the best set of predictors for each part of the model, a feature selection search strategy based on *Akaike Information Criterion* will be utilized, in which the set of predictors are included in the *full model* and at each step of the iterative process, a predictor is dropped out. To assess the fitting performance of the final model, well-known evaluation metrics for regression (e.g. mean and median squared, absolute and percentage errors) and classification tasks (*accuracy*, *F*-*measure*, *G*-*mean*, *precision* and *recall*) will be used, whereas for the evaluation of the prediction performance of the model, data-generating schemas (i.e. *holdout* and *k-fold cross-validation*) that split the available dataset into training and test sets will be performed. In addition, graphical evaluation of model’s performance will be assessed through appropriate visualization methods, such as *Receiver Operating Characteristic* (ROC) and *Precision-Recall* curves for the zero-hurdle part and *Regression Error Characteristic* (REC) curves for the truncated count part.

*Survival analysis* methods will be also performed for examining patients at follow-up period. More specifically, the non-parametric *Kaplan–Meier* analysis will be conducted for graphically evaluating the survival function of patients, while *log-rank tests* will be conducted for investigating effects of different factors on survival distribution. Finally, *Cox Regression* analysis will be performed to build a multivariate regression model between several predictors and the survival time of patients.. Statistical analysis will be performed via the R statistical programming language. In all tests a difference will be considered as statistically significant when p-value (significance) will be less than 0.05, while all conducted tests will be two-tailed (non-directional).

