### Statistical considerations

#### Sample size estimation and endpoints of the study

The primary endpoint of the study is to discover potential correlations of the SYNTAX score with patients' genomic profile and create a blood-based gene expression test (genetic SYNTAX score) which could accurately identify patients at high risk for CAD of moderate or high severity. For the estimation of the sample size the G*Power [25, 26] and Epi Info (StatCalc) [27] software tools were used. To this regard, we made use of the exact sampling distribution of the squared multiple correlation coefficient implemented in G*Power assuming 250 predictors, a two-tailed test, power of 0.9, significance level of 0.05, ρ^2^ = 0.13 and a ratio of unexposed to exposed equal to 2 (based on a pilot study on 100 patients). The initial sample size was finally increased by 10% because of the possibility that some patients might be lost to follow-up. Hence, we aim for a total sample of 1080 patients.

Secondary endpoints of the study are the development of a panel of genetic markers that, in conjunction with clinical parameters, could strongly predict the occurrence of MACCE or any bleeding events during follow up.

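### The rank tests are said to address population medians of SYNTAX, but with excess zeros a significant result does not establish that medians differ

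*Protocol article*

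**What the plan says.** The Statistical analysis section states that the response, the SYNTAX score, "presents a heavily-skewed and non-normal distribution with an excess number of zeros". It gives this as the reason for using non-parametric tests, and names what they are to investigate: "main effects of categorical variables on the population median values of the response variable". The tests are Mann–Whitney, and Kruskal–Wallis "followed by pair-wise comparisons through Mann–Whitney test using" a Bonferroni correction. No assumption about the shape of the score in the compared groups is stated.

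The same section sets the significance rule: "In all tests a difference will be considered as statistically significant when p-value (significance) will be less than 0.05". The summaries it lists for numerical data are mean, standard deviation, median, minimum and maximum.

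Model building then rests on a hurdle model, with one part for zero against positive scores and another for the size of the positive scores.

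**The concern.** Mann–Whitney and Kruskal–Wallis respond to whether scores in one group tend to exceed those in another. Reading a rejection as a difference in medians needs a further restriction on how the groups may differ. A non-negative score with a spike at zero in each group, and a spike of different size in each, does not supply that restriction. The groups can differ in the share of zeros, in the positive scores, or in both, and the median may register none of this.

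The property cited to justify the tests, "heavily-skewed and non-normal distribution with an excess number of zeros", is therefore the one that undermines the stated target. If the sentence is followed literally, a significant test could be read as a difference in median SYNTAX where there is none. A reader could also meet medians of 0 and 0 beside p < 0.05, without learning whether the factor relates to having any disease or to its extent. The primary endpoint seeks correlations between SYNTAX and genomic profile, and genotype is categorical, so these tests are a natural first look at the main question.

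**Working it through.** **Is there a figure in the plan to reproduce?** No. The article gives neither a zero share nor a power figure for the rank tests. The total of 1080 serves below only to set realistic group sizes.

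**Inputs from the article**
- Total sample: "Hence, we aim for a total sample of 1080 patients" (Sample size estimation and endpoints of the study).
- Group split: "a ratio of unexposed to exposed equal to 2" (same section), so 1080/3 = 360 and 720.
- Two-sided test at 0.05 (Statistical analysis).

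**Assumptions**
- The zero shares in the two groups, a for n₁ = 360 and b for n₂ = 720.
- The same distribution of positive scores in both groups.

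**Step 1: what the test measures.** The quantity behind Mann–Whitney is θ = P(X>Y) + 0.5·P(X=Y). With identical positive parts,

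θ = (1−a)b + ab/2 + (1−a)(1−b)/2 = 0.5 + (b−a)/2.

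For a = 0.60 and b = 0.70: θ = 0.28 + 0.21 + 0.06 = 0.55. Both population medians are 0, because more than half of each group scores zero. The median difference is 0 while θ is not 0.5.

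**Step 2: how often the test rejects.** Under the null, with the tie correction for the zeros (ties among positive scores ignored), the variance of the estimated θ is about (N+1)/(12·n₁·n₂) × (1 − p³), where p is the pooled zero share.

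- 60% v 70%: p = (216 + 504)/1080 = 0.667, p³ = 0.296. Variance = 1081/(12·360·720) × 0.704 = 0.000245, standard error 0.0156. z = 0.05/0.0156 = 3.20. Power ≈ Φ(3.20 − 1.96) = 0.89.
- 55% v 65%: θ = 0.55 again, p = (198 + 468)/1080 = 0.617, p³ = 0.235. Standard error 0.0163, z = 3.07. Power ≈ Φ(1.11) = 0.87.

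**Step 3: simulation.** Two-sided Mann–Whitney with tie correction, 360 v 720, 2000 samples per row, lognormal positive part:

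| Zero shares (360 v 720) | Rejects | Rejects with both sample medians 0 |
|---|---|---|
| 60% v 60%, same positive scores (null) | 5.1% | 5.1% |
| 55% v 65%, same positive scores | 86% | 83% |
| 60% v 70%, same positive scores | 90% | 90% |
| 55% v 75%, same positive scores | 100% | 96% |
| 60% v 60%, positive medians about 18 v 14 | 14% | 14% |

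Separate simulations of the 60% v 70% case, including runs with a negative-binomial positive part, gave between 86% and 90%, which brackets the analytic 89%.

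**Step 4: does the fault need half zeros?** The 0 v 0 picture does, but the logical point does not. As a constructed example, take zero shares of 20% and 40%. In both groups let the lower half of the distribution end at a score of 9 and the upper half start at 10. The population median then lies between 9 and 10 in each group, yet θ = 0.55 again (0.12 + 0.015 + 0.04 + 0.25 + 0.125) and Mann–Whitney rejects in 80% of samples.

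**The case against.** The strongest reply is that little depends on the phrase. The hurdle model, which is meant to build the score, already asks separately about any disease and about its extent, with its own predictors and performance curves for each part. The rank tests are a univariate step before it. This reply stands, and it removes most of the harm, but it does not correct the stated target of the univariate tests.

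The second reply is that the 0 v 0 result rests on a zero share that the article never gives. An excess of zeros relative to a count model need not mean half the patients, and the article gives no mix of preoperative, chronic and acute patients. This also stands, so the rejection rates are illustrations. Below half zeros the case is weaker: if only the zero share differs and the positive scores are alike, the medians of the whole score generally do differ, and a conclusion about medians would be true.

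Three stronger readings are tempting, and the document does not support them:
- **That the tests are invalid.** They are not. Under the null they reject at about 5%.
- **That every significant result will be reported as a median difference.** The article lists the median among its summaries but sets no such reporting rule. It only names the median as the target.
- **That rank tests can never speak to medians outside a pure shift in location.** This is too strong. Rank tests are unchanged by monotone transformation, so a pure change of scale in a positive continuous score would also allow the median reading. Neither case covers a spike at zero whose size differs between groups.

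**Conclusion.** The point holds as a mismatch between the stated target and the tests, and it is minor. The article says affirmatively that the rank tests concern population medians, and nothing elsewhere in it corrects this. For a score with a zero spike that varies between groups, a rejection supports a difference in distribution and does not by itself establish different medians.

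The visible symptom, significance with both medians 0, arises in about 86–90% of samples at 60% v 70% zeros with 360 v 720 patients and identical positive scores. That range is conditional on about half or more of each compared group scoring zero, which is an assumption. P-values, sample size and the hurdle model are unaffected. What changes is the conclusion that a univariate result permits.

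**What to change.** Replace the reference to population median values with a comparison of the distribution of the SYNTAX score between groups (stochastic ordering), and word conclusions to match: scores tend to be higher in one group than in another.

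Beside these tests, report for each group the percentage with SYNTAX = 0 and the median among patients with SYNTAX > 0. The two figures correspond to the two parts of the hurdle model, so the univariate and modelled results can be read together. A probability index, P(X>Y) + 0.5·P(X=Y), with its interval for key comparisons is optional and goes beyond what the error requires.

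The cost is one reworded sentence and some extra table columns, more noticeable if tables are produced for many of the 228 SNPs. The tests, their p-values and the sample size stay as they are.

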## Methods

### Study design and population

GESS (ClinicalTrials.gov Identifier: NCT03150680) is an ongoing prospective, single‐center, cohort study enrolling patients undergoing coronary angiography.

Ethical approval was obtained from the Scientific Committee of AHEPA University Hospital (reference number 309/11–05-2017). Written informed consent will be obtained from each patient prior to study enrollment and the trial procedures conform with the Declaration of Helsinki [17].

GESS study is designed to enroll 1080 consecutive adult patients admitted to AHEPA University Hospital of Thessaloniki, Greece and undergoing coronary angiography for clinical purposes. Coronary angiography can be performed either on an emergency basis or scheduled. For the purpose of this research, patients with history of prior percutaneous coronary intervention or coronary artery bypass grafting and patients unwilling to provide informed consent will be excluded from the study. The selection criteria of the study are presented in detail in Table 1.

**Table 1 Tab1:** Eligibility criteria for the enrollment in the GESS study

Inclusion criteria	Exclusion criteria
Patients undergoing coronary angiography	Medical history of prior coronary revascularization procedure
Age > 18 years old	Cardiopulmonary arrest at admission
Informed consent for study participation	Severe concurrent disease with life expectancy less than 12 months

Pre-specified clinical data, including demographic characteristics, medical history, medication and clinical presentation will be recorded for the entire study population by research study coordinators under standardized methods. Accordingly, study participants will be classified into 3 main subsets, based on their clinical presentation: 1. patients undergoing preoperative coronary angiography without symptoms suggestive of CAD, 2. patients with chronic coronary syndrome, and iii. patients with acute coronary syndrome.

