### Genotyping and bioinformatic analysis

Peripheral whole blood will be collected and labeled with a unique barcode to ensure anonymization and unbiased assessment. High quality genomic DNA will be extracted using commercial kits (Qiagen) and will be quantified by spectrophotometry using Nanodrop 1000 (Thermo Fisher). Ultrasensitive targeted NGS of extracted DNA (40 ng) will be performed using custom QIAseq Targeted DNA Panel (Qiagen) containing primers for the enrichment of the 228 SNPs of interest. The produced molecularly barcoded libraries will be quantified by Qubit 3 Fluorometer (Invitrogen) and real time PCR (QIAseq Library Quant Assay kit). Sequencing will be performed by sequencing by synthesis (SBS) chemistry on MiniSeq Platform of Illumina using the MiniSeq Mid Output Kit (300-cycles). The generated NGS data (in fastq format) will be analyzed with the CLC Genomics Workbench (Qiagen) bioinformatics software and the genotype of each SNP will be determined.

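### Bonferroni on the pairwise tests after Kruskal–Wallis is valid but needlessly conservative; Holm keeps the same 5% familywise limit with more power

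*Protocol article*

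**What the plan says.** In the protocol article, section Statistical analysis, non-parametric tests are planned for the "investigation of the main effects of categorical variables on the population median values of the response variable", the SYNTAX score. The reason given is that the score "presents a heavily-skewed and non-normal distribution with an excess number of zeros". Mann–Whitney and Kruskal–Wallis are named, the latter "followed by pair-wise comparisons through Mann–Whitney test using" Bonferroni's correction. The same section says "a difference will be considered as statistically significant when p-value (significance) will be less than 0.05" and makes every test two-sided.

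The procedure covers categorical variables of any number of levels. One explanatory factor is explicitly three-level: under Study design and population, "study participants will be classified into 3 main subsets, based on their clinical presentation". SNP genotypes may be three-level too, but the article does not state how they are coded.

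The text does not say that the pairwise tests are run only when Kruskal–Wallis is significant.

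**The concern.** Bonferroni divides 0.05 by the number of pairs and holds every pair to that level. This guarantees 5% familywise error, but other procedures give the same guarantee and reject more. With three groups, a significant Kruskal–Wallis test can itself provide most of the protection, so adding Bonferroni pays twice. At stake is the chance of detecting true pairwise differences in SYNTAX score, for example between presentation subsets.

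**Working it through.** **Inputs from the article:** two-sided 0.05; three presentation subsets; total sample 1080; skewed outcome with excess zeros.

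**Assumptions:** Bonferroni runs over the pairs within one factor. Group sizes, zero fractions and shifts are not in the article and are set below. The article gives no power or error figure for these tests (its sample-size calculation concerns a multiple correlation, "assuming 250 predictors, a two-tailed test, power of 0.9, significance level of 0.05"), so there is no stated figure to reproduce.

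**1. Level per pair.** Three groups give three pairs: 0.05/3 = 0.0167, critical value 2.394 instead of 1.960.

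**2. Power of one pair (normal approximation, no gate).** Power at 0.0167 = Φ(1.960 + z(power at 0.05) − 2.394).
- 70%: Φ(1.960 + 0.524 − 2.394) = Φ(0.090) = 54%
- 80%: Φ(1.960 + 0.842 − 2.394) = Φ(0.408) = 66%
- 90%: Φ(1.960 + 1.282 − 2.394) = Φ(0.848) = 80%

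Restoring 80% takes ((2.394 + 0.842)/(1.960 + 0.842))² = 1.33, or about 33% more patients in that pair.

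**3. Why three groups are special.** If any two of the three hypotheses of equal distributions are true, all three groups are equal. The only intersection hypothesis is therefore the global null, which Kruskal–Wallis tests at 0.05. By closure, a significant Kruskal–Wallis test followed by pairwise tests at 0.05 controls familywise error at 5%.

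**4. Familywise error by simulation.** N = 1080, about 35% zeros, skewed positive scores, 10,000 runs, Kruskal–Wallis gate in both columns, three sets of group sizes.

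| Truth | Pairs at 0.05 | Pairs at 0.0167 |
|---|---|---|
| All three equal | 4.7–5.0% | 3.6–4.1% |
| Two equal, third far away | 5.2–5.4% | 1.7–1.8% |

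The simulation standard error is √(0.05 × 0.95/10,000) = 0.22 points, so 5.4% is about two standard errors above 5%. A separate rerun gave 4.9–5.4% and 4.3–5.7% for the unadjusted column.

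**5. Pairwise power with the gate, 5,000 runs.** "One shifted": the third group has 27% zeros and higher positive scores. "Graded": 40%, 35% and 28% zeros with rising positive scores. Pairs are in the order 1–2, 1–3, 2–3; for "one shifted", only the two truly different pairs are shown.

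| Group sizes | Effect | Pairs at 0.05 | Pairs at 0.0167 | Loss (points) |
|---|---|---|---|---|
| 360/360/360 | One shifted | 70.9, 69.9% | 60.6, 59.2% | 10, 11 |
| 360/360/360 | Graded | 33.4, 94.8, 66.8% | 19.5, 93.5, 49.8% | 14, 1, 17 |
| 540/432/108 | One shifted | 35.7, 34.0% | 29.8, 27.9% | 6, 6 |
| 540/432/108 | Graded | 40.9, 72.0, 36.6% | 27.0, 65.0, 22.7% | 14, 7, 14 |
| 100/400/580 | One shifted | 43.0, 80.8% | 27.7, 73.6% | 15, 7 |
| 100/400/580 | Graded | 17.2, 74.1, 75.6% | 7.8, 61.4, 63.9% | 9, 13, 12 |

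Groups of 216/540/324 (1,500 runs) gave 63% against 56% with one group different and 70% against 54% with all three different.

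**6. Holm.** With three pairs, the ordered p-values are compared with 0.05/3, 0.05/2 and 0.05, stopping at the first failure. No threshold is below Bonferroni's, so Holm rejects everything Bonferroni rejects. It controls familywise error at 5% for any number of groups, without a gate. In simulation it held 5% ungated and gained up to about 9 points of pairwise power over Bonferroni.

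**7. Where unadjusted tests fail.** For three equal-sized groups without a gate, the studentized range gives P(range > 1.960 × √2) = 12.2% familywise error, against 4.4% with Bonferroni. With four groups forming two equal pairs, the gate alone gives 9.7%, matching 1 − 0.95² = 9.75%.

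**The case against.** The strongest reply is that nothing here is wrong. Bonferroni after Kruskal–Wallis is conventional and valid, and choosing among valid procedures could be left to the analysis plan. It stands that this is an improvement and not an error. But the article does fix Bonferroni, and a procedure with the same guarantee that rejects at least as much is available at no cost.

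Four further objections have weight:

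- **The gate.** A reader might infer from the word order that pairwise tests follow only a significant Kruskal–Wallis result, so that Bonferroni can simply be dropped. The text does not say so. On an ungated reading Bonferroni is what controls the error (4.4% against 12.2%).
- **Error control.** A reader might infer that Bonferroni brings no gain in error control at all. Realised error does fall, to 1.7–1.8% with one null pair. What is absent is any gain beyond the 5% limit already met.
- **Medians.** The article words the hypotheses as medians, while the closure argument needs equal distributions. In a simulation with two groups of unequal dispersion but no Mann–Whitney shift, gated unadjusted error reached 7.3–8.6% when the more dispersed group was the smaller, against 2.8–3.4% with Bonferroni; other allocations gave 2.9–4.5% unadjusted. This is largely Mann–Whitney misstating its own level: 7.3–8.6% is 1.5 to 1.7 times 5%, and 2.8–3.4% is 1.7 to 2.0 times 1.67%. It does not justify Bonferroni, but it does require the hypotheses to be worded as distributions.
- **Direction.** No correction across the 228 SNPs is stated for these tests, so relaxing the within-factor correction could look unhelpful. Within-factor Bonferroni does not address that multiplicity either; it is a separate and larger matter.

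**Conclusion.** The point holds as a minor, free improvement. Within a factor, Bonferroni gives no gain beyond the 5% familywise limit. Compared with a gated closed test for three groups, it costs roughly 1 to 17 points of pairwise power. The size rests on assumed group sizes, zero fractions and effects; the direction does not. Holm recovers part of that loss (up to about 9 points) without needing a gate.

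Two stronger conclusions are not supported. The three-group shortcut does not extend to factors with four or more levels, where a gate alone lets the error approach 10%. Nor does this touch the main modelling: the hurdle model is built by backward elimination on the Akaike criterion from the full model, and no univariate p-value is said to feed it. The Kruskal–Wallis tests themselves are unchanged.

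**What to change.** Replace Bonferroni with Holm's procedure for the pairwise Mann–Whitney comparisons of any factor. This alone is sufficient, with or without a gate.

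Optionally, for three-level factors such as clinical presentation, use unadjusted pairwise tests at 0.05 instead, provided the plan states both of these:
- pairwise tests are run only after a significant Kruskal–Wallis test;
- the hypotheses are equality of distributions, not of medians.

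If a stricter level is set across factors, for example across the SNPs, use that level for both the Kruskal–Wallis and the pairwise step.

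The cost is a sentence in the analysis plan, with no further patients or data.

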## Abstract

**Background:**

Coronary artery disease (CAD) remains one of the leading causes of mortality worldwide and is associated with multiple inherited and environmental risk factors. This study is designed to identify, design, and develop a panel of genetic markers that combined with clinical and angiographic information, will facilitate the creation of a personalized risk prediction algorithm (GEnetic Syntax Score—GESS). GESS score could be a reliable tool for predicting cardiovascular risk for future adverse events and for guiding therapeutic strategies.

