The SYNTAX score is the best-known scoring algorithm to evaluate CAD complexity as a comprehensive angiographic grading tool taking into consideration anatomic risk factors [16]. According to the extent of CAD, this score facilitates the objective guidance of decision-making between coronary artery bypass grafting (CABG) surgery and percutaneous coronary intervention (PCI). Despite, the SYNTAX score relies on invasive coronary angiography findings and the discovery of risk stratification algorithms that facilitate non-invasive estimation of CAD complexity could alter the prognostic plan in patients with CAD.

The rationale behind this prospective study is to associate, for the first time, the severity of CAD, as assessed by the SYNTAX score, with patients’ genomic profile in a real-world setting of patients undergoing coronary angiography [16]. The desirable goal is to corroborate genomic and pharmacogenetic research on CAD exploring the potential clinical association of 228 selected SNPs with CAD and individualized response to clopidogrel and statin therapy, which could disentangle gene expression alterations in blood of patients with CAD. Ultimately, the GESS trial aspires to develop a genetic SYNTAX score that could non-invasively enable the identification of patients with complex and severe CAD after a blood-based gene expression analysis. This study is designed to contribute to recent calls for implementing genotype-guided precision medicine decisions, by aiding the clinicians to achieve improved prediction and therapy outcomes for CAD patients [3].

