Nevertheless, GWAS have only provided population-attributable risk data and could not be transferred to an individual with CAD. During the last decade, the advent of NGS has enabled researchers to perform parallel analyses of hundreds of genes in an unbiased approach [8]. This is attracting widespread attention enhancing CAD translational study and aiding to close the gap between genotype and phenotype. In 2013 the CARDIoGRAMplusC4D Consortium reported that targeted sequencing with NGS can discover rare variants with high sensitivity, rendering NGS an essential genetics approach in the post-GWA study era [38].

Apart from genetic mapping, GWAS and NGS studies have also explored the clinical utility of genetic biomarkers for the creation of genetic risk scores [10, 11, 36, 41]. These algorithms would ideally predict the severity of CAD and the subsequent adverse outcomes aiming to identify patients with potential benefit from preventive care. For their development, researchers have examined the prognostic value of blood-based genetic panels, in comparison with imaging (myocardial perfusion imaging or coronary computed tomography angiography), angiographic (visual or quantitative assessment of coronary artery stenosis or Gensini) or clinical (GRACE) predictive scores [12, 15, 42–44]. COMPASS and PREDICT trials created 2 gene-expression scores outperforming clinical factors and non-invasive imaging in discriminating patients with > 50% stenosis [45, 46]. Despite, Labos et al. reported that the addition of their developed polygenic risk score to the GRACE risk score could not significantly improve risk classification in acute coronary syndrome admissions [42]. Moreover, weighted multi-locus risk scores have been created to predict recurrent vascular events or statin efficacy and atherosclerotic burden alterations in CAD populations [10, 47–49]. Nevertheless, limited data exist about the utility of genetic risk scores for the prediction of MACCE [11–13, 41].

To the best of our knowledge, GESS is the first study yet to investigate the association of such a large number of candidate SNPs (228) with SYNTAX-score-based CAD complexity. To this end, GESS emerges as a part of a research project aspiring to complement traditional risk factor assessment with panels of significant metabolomic and genomic biomarkers [50, 51]. The co-evaluation of novel risk factors and the complexity of CAD could significantly expand the concept of cardiovascular precision medicine.

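### As written, the plan evaluates only one AIC-selected model with no clinical-only reference, so its metrics do not show what the SNPs add to the clinical data

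*Protocol article*

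**What the plan says.** **Model building (Statistical analysis).** The SYNTAX score is modelled by a hurdle model with a zero part and a truncated count part. The "identification of the best set of predictors for each part of the model" is done by AIC: "the set of predictors are included in the *full model* and at each step of the iterative process, a predictor is dropped out". No predictor is named as kept regardless of AIC, and the candidate predictors are not listed.

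**Evaluation (same section).** "To assess the fitting performance of the final model, well-known evaluation metrics for regression" and for classification are used. For predictive performance, "data-generating schemas (i.e. *holdout* and *k-fold cross-validation*) that split the available dataset into training and test sets will be performed". ROC and precision-recall curves are named for the zero-hurdle part. No second model is mentioned.

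**Candidate predictors.** The sample size estimation assumes 250 predictors; the genotyping section describes a panel for 228 SNPs.

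**Clinical data (Study design and population).** Demographics, history, medication and presentation are recorded for the entire population, and "study participants will be classified into 3 main subsets, based on their clinical presentation".

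**Aim.** The primary endpoint asks for correlations between SYNTAX and the genomic profile, and for a test that accurately identifies patients at high risk of moderate or high severity disease. The Discussion places the study in a project "aspiring to complement traditional risk factor assessment with panels of significant metabolomic and genomic biomarkers".

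**The concern.** A score called genetic is useful to a clinician only if it tells more than age, sex, history and presentation already do. The Discussion applies this standard to others: it credits two gene-expression scores with outperforming clinical factors and imaging, and notes that adding a polygenic score to GRACE did not significantly improve risk classification.

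The plan yields the performance of one selected model. If clinical and genetic variables are both candidates, good performance could come wholly from the clinical ones and still be reported as that of a genetic SYNTAX score. Readers might also take the SNPs that survive selection as confirmed contributors, which AIC does not justify with this many candidates.

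**Working it through.** **1. Plan's own figure.** The plan states no figure for the SNP increment. Its only related calculation is the test of the squared multiple correlation for the whole set: 250 predictors, ρ² = 0.13, α = 0.05, power 0.90. The exact random-predictor calculation gives 657 patients, or 723 after adding 10% (716 and 788 with 0.025 in the upper tail), not 1080. That mismatch is a separate question and does not decide this one. What matters here is that the test covers all predictors jointly. With 1080 / 1.1 ≈ 982 evaluable patients its power is about 99.8%, and this would be so even if the whole 0.13 came from clinical variables.

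**2. Are clinical variables in the pool?** 250 − 228 = 22 non-SNP predictors, if each SNP takes one term. This is an inference, because no list is given.

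**3. What AIC retention means.** A one-degree-of-freedom term stays if its likelihood-ratio statistic exceeds 2. For a null term, P(χ²₁ > 2) = 0.157. Expected null SNPs retained: 228 × 0.157 ≈ 36.

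**4. What the final model's fit shows.** Simulation with a linear model as stand-in for the hurdle model: 982 patients, 22 clinical variables (three with an effect, joint R² 0.13), 228 SNPs with no effect, backward AIC, 100 runs.

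| Mean over runs | AIC-selected model | Clinical-only model |
|---|---|---|
| SNPs retained | 46 | 0 |
| R² in the fitted data | 0.27 | 0.15 |
| R² in new data | -0.05 | 0.11 |

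The retained count exceeds 36 because 250 terms fitted to 982 patients understate the residual variance. Fit metrics would favour the model that predicts worse. Honest cross-validation would expose poor absolute performance, but without a base model in the same folds it cannot attribute good or poor performance to the SNPs.

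**5. Could the increment be measured at this size?** Partial F test of 228 SNPs over 22 clinical predictors, total R² fixed at 0.13, f² = increment / 0.87, noncentrality N·f², N = 982. The split between clinical and genetic R² is an assumption.

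| SNP increment in R² | Power | N for 90% power |
|---|---|---|
| 0.10 | 98.5% | 762 |
| 0.08 | 93.5% | 912 |
| 0.065 | 84.0% | 1087 |
| 0.05 | 67.2% | 1368 |
| 0.03 | 36.9% | 2182 |

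The comparison is thus feasible for a large genetic share and weak for a small one. This test is only a guide to feasibility; the fix below uses out-of-sample differences.

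**6. Is the evaluated outcome the target?** The plan's categories are 0–22, 23–32 and above 32, so moderate or high severity means SYNTAX ≥ 23. The ROC curve is specified for the zero part, which separates zero from positive scores.

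**The case against.** **This is detail for the SAP.** Predictor lists and reference models are often left there, and the SAP is not shown. That is fair for the list. But the article fixes the selection rule, the object of evaluation, the metrics, the validation scheme and the plots; what it fixes is a one-model evaluation.

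**No increment is promised.** The primary endpoint asks for correlation and accurate identification, and the phrase about complementing risk factors concerns the wider project. This stands as a limit on how strongly the aim can be invoked. The Discussion's own yardstick for earlier scores is nevertheless gain over clinical tools.

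**The model may contain SNPs only.** The primary product is described as blood-based, and clinical parameters are named only for the secondary endpoints. In that case the metrics would describe the SNPs alone, but their gain over clinical data would still be unreported.

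A reader might infer more than the document supports:

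- *That the trial cannot show added value.* It can: clinical data are recorded for everyone, and the comparison needs no new data.
- *That AIC is likely to discard age, sex or presentation.* At N = 982 the chance of dropping a one-degree-of-freedom term is about 4% at partial R² 0.01 and 21% at 0.005; the true clinical predictors were kept in every simulated run.
- *That the presentation subsets go unused.* They are not named in the analysis, but the planned Kruskal–Wallis tests of categorical variables could cover them.
- *That the score is circular, since the abstract joins* "a panel of genetic markers that combined with clinical and angiographic information" *while the Background says the score* "could non-invasively enable the identification of patients with complex and severe CAD". The abstract's sentence reads naturally as the score for future events, where angiographic input is legitimate. No text makes angiographic variables predictors of SYNTAX.
- *That adjusting the SNP tests would gain a definite percentage in precision.* The document gives no share of SYNTAX variance explained by baseline variables, so any such figure would be assumed.

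**Conclusion.** The point holds in limited form: the analysis as written has no output that isolates what the SNPs add to recorded clinical data, and neither good fit of the final model nor SNP retention can stand in for one. About 36 of 228 null SNPs would be expected to survive AIC by the large-sample rule, and 46 did on average in the simulation, with an apparent R² advantage of 0.12 (0.27 − 0.15) that became a deficit of 0.16 in new data (0.11 + 0.05).

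This rests on three assumptions: that the roughly 22 remaining predictors are clinical; that a linear model is an adequate guide to the hurdle model's behaviour; and that the null-SNP scenario is a bounding case rather than a forecast. The absence of a comparator depends on none of them. It should be corrected before analysis, but it does not call for redesign.

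**What to change.** 1. Pre-specify a base model with age, sex and clinical presentation kept in both hurdle parts.
2. Fit base and base + SNP models in the same cross-validation folds, repeating the selection step inside each fold.
3. Report the out-of-sample difference between the two with a confidence interval as the measure of genetic value. Include discrimination for SYNTAX ≥ 23 alongside zero versus positive.
4. Make the same base versus base + SNP comparison for the Cox models of follow-up events.
5. State that retention by AIC is not in itself evidence that a SNP contributes.

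The cost is analysis-plan wording and one extra model fit per outcome; no further data are needed. The downside is that the genetic contribution may look small, and if it is small in truth the interval around it will be wide at this sample size.
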